**STUDY DESIGN**

This is a single-center, randomized, parallel group, comparison of preemptive versus empiric antifungal therapy (e.g., standard care) for the management of suspected IC in SICU patients (**Figure 1**). Adult patients treated in the Duke SICUs for at least 3 days, and expected to require at least an additional 2 days of intensive care, will be approached for enrollment into the study. Patients providing informed consent will be stratified according to APACHE II score and randomly assigned in a 3:1 fashion to active surveillance with preemptive therapy or standard care. At Duke University, standard care is empiric antifungal therapy based on physician discretion.

**Active surveillance/ preemptive therapy group**

Subjects in this arm of the study will have serum drawn twice a week for BDG testing while in the SICU, with the results of the test reported to the managing clinicians in real-time. Subjects will receive intravenous (IV) anidulafungin should the β-D-glucan exceed 60 pg/ml on a single determination. A positive test cut-off of 60 pg/ml was selected based on the observation that 81% of patients with IC will have a positive test at this level(25). Preemptive therapy will continue for a minimum of 14 days or for as long as the subject remains in the ICU up to a maximum of 28 days duration.

If the BDG test turns positive and preemptive therapy is initiated, serum will then be collected every other day to assess the kinetics of the BDG test on anidulafungin treatment. Kinetic monitoring will continue until the test becomes negative at which time twice weekly assessments will be resumed and continue for as long as the patient remains in the SICU. Samples collected while patients are receiving anidulafungin will be batched and run retrospectively. Clinicians will not have these results made available for use in real-time. However, once preemptive anidulafungin therapy is completed and the drug has been stopped, biweekly monitoring with results reported to the medical team will be resumed. Subjects, however will not be restarted on anidulafungin should the test again turn positive after a course of preemptive therapy is completed.

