**Chart of Study Procedures**

| **Procedure** | **Screening/Baseline** | **Weekly** | **Bi-weekly** | **Treatment** | **SICU Discharge** |
| --- | --- | --- | --- | --- | --- |
| **Informed Consent** | **X** |  |  |  |  |
| **Clinical Information** | **X^a^** | **X^a^** |  |  |  |
| **Physical Examination** | **X** |  |  | **X^b^** |  |
| **APACHE II Score Assessment** | **X** |  |  | **X** |  |
| **IFI Assessment^c^** | **X** | **X** |  |  | **X** |
| **Medication Review** | **X** | **X** |  |  |  |
| **Β-D-Glucan^d^** | **X** |  | **X** | **X** |  |
| **Fungal Culture^e^** | **X** |  |  | **X** | **X** |
| **Fungal Susceptibility^e^** | **X** |  |  | **X** | **X** |
| **Β-hCG** | **X^f^** |  |  |  |  |
| **LFTs^g^** | **X** |  |  | **X** |  |
| **RNA collection^h^** | **X** |  | **X** | **X** |  |
| **Blood Culture^i^** |  |  |  | **X** |  |

^a^Demographics, baseline conditions, pertinent past medical history at baseline followed by weekly assessment for evidence of IFI and for IC risk factors.

^b^Obtain within 72 hours of 1^st^ dose of study drug and weekly there after while receiving anidulafungin.

^c^ Vital signs, clinical signs and symptoms, routine laboratory tests, culture results, radiographic findings, and/or biopsy reports indicative of IFI.

^d^ Only BDG results for subjects in the active surveillance/preemptive therapy arm will be reported to clinicians in real-time. BDG testing for subjects receiving usual care will be performed in batches, retrospectively. Subjects on anidulafungin will have the BDG test performed every other day until negative to determine kinetics on therapy. Samples collected for BDG kinetics will be batch tested retrospectively, therefore the results will not be reported to clinicians.

^e^ Oral swish and spit or ETS aspirate (from those subjects requiring mechanical ventilation) to assess for fungal colonization will be performed at baseline, after the completion of any systemic antifungal therapy, and at SICU discharge. Susceptibility testing to echinocandins and fluconazole will be performed on each isolate recovered. Results will not be reported to the care providers.

^f.^ Pregnant women will be excluded from the study.

^g^ LFTs will be collected at baseline and weekly on anidulafungin. LFTs include: total bilirubin, alkaline phosphatase, AST, and ALT

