**All Subjects**

The following procedures will be performed for all study subjects for the duration of the SICU stay:

- Serum red-top BDG and a PAX Gene tubes will be obtained 2 times/week (generally Monday and Thursdays) with the routine early morning blood work by the SICU nursing staff. Both phlebotomy tubes will be sent directly to the Duke Clinical Microbiology Laboratory. BDG results will be made available in real-time (within 24–72 hours) via a phone call directly to the clinician (surgical house staff and unit pharmacist) caring for the study subject assigned to preemptive therapy. BDG specimens obtained from patients assigned to empiric therapy (standard care) will be batched and tested at the end of study and the clinicians will not be made aware of the results. All RNA analyses will also be performed retrospectively for research purposes only.

*Patients in the active surveillance/preemptive therapy arm may have BDG testing performed on other days if the providers feel that the result would immediately impact initiation of antifungal therapy. The test will be available daily Monday through Friday.

- IFI assessments will be made weekly (EORTC/MSG criteria for proven or probable IFI will be applied [**Tables 3 & 4**]) and documented on the CRF.
- Supporting evidence of IFI obtained as part of routine care will be recorded weekly (i.e. routine laboratory testing, microbiology and blood culture results, imaging studies, biopsy reports) and documented on the CRF.
- Clinical risk factors for IC will be documented weekly (**Table 1**) and documented on the CRF.
- Factors known to be associated with false positive BDG tests will be documented weekly (**Table 2**) and documented on the CRF.
- Concomitant antimicrobials and immunosuppressive drugs will be documented weekly on the CRF.
- AEs will be recorded weekly and documented on a dedicated CRF.

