**DIAGNOSTIC TESTS**

Serum for BDG and a PAX Gene tube will be obtained along with the routine morning SICU blood work twice weekly on Monday and Thursday. Samples will be sent to the Duke Clinical Microbiology Laboratory. Serum for BDG will be processed by the study technologist within 6 hours of collection. BDG will be performed by the study technologist and the results reported immediately to the SICU for patients in the active surveillance arm. Serum from patients in the standard care arm will be stored at -70°C and tested at the completion of the study. The BDG assay will be performed as per manufacturer’s instructions, using a positive cutoff of ≥ 60 pg/mL. Other study related laboratory tests (i.e., LFTs) will be performed by the Duke Clinical Laboratories. Blood cultures, surveillance fungal cultures, and susceptibility testing will be performed by the Duke Clinical Microbiology Laboratory as per standard operating procedure. All but the surveillance fungal culture will be reported in the medical record for clinical use. The PAX Gene collection system can remain at room temperature for up to 72hrs, samples will be processed by [name] and all RNA analyses will be performed retrospectively after study completion.

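### In the preemptive arm, BDG testing switches from real-time to batched retrospective runs when anidulafungin starts, so any assay shift is confounded with treatment for BDG kinetics and BDG response

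*Protocol*

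**What the plan says.** **Before treatment.** Under Diagnostic Tests: "BDG will be performed by the study technologist and the results reported immediately to the SICU for patients in the active surveillance arm". The All Subjects section allows 24 to 72 hours for the result.

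**On treatment.** The section on the active surveillance arm says "Samples collected while patients are receiving anidulafungin will be batched and run retrospectively", and footnote d of the Chart of Study Procedures agrees: "Samples collected for BDG kinetics will be batch tested retrospectively, therefore the results will not be reported to clinicians". The purpose is stated: "serum will then be collected every other day to assess the kinetics of the BDG test on anidulafungin treatment".

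**After treatment.** Once the drug has been stopped, "biweekly monitoring with results reported to the medical team will be resumed".

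**Use of the values.** Under End Point Definitions (Clinical Response), response to preemptive therapy requires a normalized BDG and resolution of any fever or attributable signs that were present. Table 5 requires resolution of the abnormal BDG alone and places the assessment at the end of treatment. Response to therapy is secondary endpoint 6.

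**Storage.** The only storage condition given for BDG serum is for the other arm: "Serum from patients in the standard care arm will be stored at -70°C and tested at the completion of the study". None is stated for the on-treatment samples, and nothing is said about keeping part of a trigger sample.

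**The concern.** Within each treated patient, two things change together: the drug starts, and the assay moves from a real-time run to a later run on stored serum. When the drug stops, real-time reporting returns. A before-and-after comparison of BDG in the same patient therefore cannot separate a drug effect from a storage or batch effect, because no sample is measured both ways.

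The comparison is made against a fixed cut-off of 60 pg/mL. Patients enter treatment on a single value above that cut-off, and many such values may lie not far above it. A modest proportional shift can then move an appreciable share of them across the line in either direction. At stake are the description of BDG kinetics on anidulafungin and the BDG component of preemptive response. The point has to be settled before enrolment, since a trigger sample that was not kept cannot be re-run later.

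**Working it through.** **The protocol's own figure.** Of 100 patients randomized 3:1, 100 × 3/4 = 75 go to active surveillance. With 25% expected positive, 0.25 × 75 = 18.75, rounded to 19. The stated 19 is reproduced, and it is the number exposed to the switch.

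**Illustration.** The protocol gives no BDG distribution, assay variability or batch effect, so these are assumptions:
- BDG is log-normal, with 25% of single tests above 60 pg/mL.
- The between-patient log-SD is 0.5 or 1.0.
- The within-patient CV is 10% or 20%, so the within-patient log-SD is √ln(1 + CV²).
- The mean log-BDG is ln 60 − 0.6745 × √(between² + within²).
- The drug has no effect.
- The second (batched) value is multiplied by a handling factor of 0.8 to 1.2.

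Among patients whose first value exceeds 60, the table gives the share whose second value is below 60 (2,000,000 simulated patients). Each range runs over the two between-patient log-SDs.

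| Batched runs read | CV 10% | CV 20% |
|---|---|---|
| 20% lower | 26-48% | 30-52% |
| 10% lower | 15-29% | 21-38% |
| the same | 7-14% | 14-27% |
| 20% higher | 1-2% | 6-12% |

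In 19 patients at CV 10%, this is about 5 to 9 at 20% lower, 1.3 to 2.7 with no shift, and 0.2 to 0.3 at 20% higher.

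**Check by hand, with no within-patient noise.** The share is 1 − P(Z > 0.6745 + ln(1/0.8)/SD) / 0.25, where ln(1/0.8) = 0.2231.
- SD 0.5: 0.6745 + 0.4463 = 1.1208; the tail is 0.131; the share is about 47.5%.
- SD 1.0: 0.6745 + 0.2231 = 0.8976; the tail is 0.185; the share is about 26.1%.

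Both match the simulated values at CV 0.

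**The opposite direction.** Suppose BDG truly halves on treatment (log-SD 1.0, CV 10%). The share below 60 is then 78% if batched runs read 20% lower, 66% with no shift, and 53% if they read 20% higher. An upward shift conceals part of a real fall.

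**What a same-batch baseline leaves.** With no shift and no drug effect, 7-14% (CV 10%) or 14-27% (CV 20%) still appear to normalize. That is regression to the mean from selecting on one high value, and it is separate from handling.

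**The case against.** The strongest reply is that no storage or batch effect is documented. The protocol specifies processing within 6 hours, a study technologist, one clinical microbiology laboratory, the manufacturer's instructions and one numerical cut-off. Repeat runs and bridging controls are often left to a laboratory manual. Nor does it say that trigger samples are run singly: draws fall mainly on two fixed days and results may take up to 72 hours, so they too may be run in groups. This stands, and it limits the point to an uncontrolled risk.

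The delay before the on-treatment batch is also unstated. The stop rule, "Kinetic monitoring will continue until the test becomes negative at which time twice weekly assessments will be resumed", needs a result while sampling continues, which fits poorly with retrospective testing. Those passages need reconciling. If batches were in fact run promptly, storage effects would be smaller, but the trigger sample would still be outside the batch.

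The scope is narrow as well. BDG kinetics is a stated purpose but appears in neither the objectives nor the endpoint list. Response is judged at the end of treatment, so a share negative on a second sample is an illustration and not the endpoint. Empiric response uses no BDG, so no between-arm BDG comparison is affected.

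Real-time values after the drug stops could serve as a comparator, but only in patients still in the unit. The synopsis has treatment run to at least 14 days or ICU discharge, whichever is longer, up to 28 days, so few patients may supply one.

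A reader might infer that primary endpoint 2, test performance, is biased in the same way. The protocol does not support that. Performance is estimated in the standard care group, where all serum is batched, so no patient changes method, and batching there is deliberate, to keep clinicians unaware of results. What remains is a caveat: accuracy is measured on stored serum while treatment is triggered by real-time results.

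**Conclusion.** The point holds in limited form. Handling changes at the start of anidulafungin in every treated patient, and the protocol provides nothing to separate that change from a drug effect. It affects BDG kinetics and the BDG part of preemptive response in about 19 patients.

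Two stronger readings are tempting and should be resisted. One is that any shift would look like a fall: only a downward shift does, and an upward one masks a fall. The other is that the results will be biased: the protocol gives neither size nor direction for a shift, so none is shown. The percentages above depend on the assumed distribution, CVs and shifts of up to 20% either way. They show only that modest shifts would matter at a fixed cut-off. This is a low-cost safeguard for a secondary endpoint, worth adopting because it cannot be added once samples are gone.

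**What to change.** In the section on the active surveillance arm and under Diagnostic Tests:
- At processing, set aside an aliquot of each preemptive-arm surveillance serum. Store it under the same condition as the on-treatment samples, and state that condition.
- Re-run each treated patient's trigger sample in the same batch as that patient's on-treatment samples.
- Use the batched trigger value as the baseline for kinetics and BDG response. The real-time result continues to decide treatment as the protocol now has it.
- Note that accuracy under primary endpoint 2 is measured on stored serum.

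Do not use these pairs to estimate agreement between real-time and batched results at 60 pg/mL. The trigger samples were chosen for lying above that value, so assay noise alone would produce disagreement.

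The cost is about 19 extra assays and freezer space. No further blood draw is needed if enough serum remains from the 3.5 ml tube already taken, which the protocol does not confirm. The change removes the handling shift but not regression to the mean, which should be acknowledged when on-treatment BDG is reported.

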**Standard care/empiric therapy group**

Patients in the standard care arm will also have biweekly blood draws for the BDG assay until ICU discharge, but the test will not be performed in real-time. Specimens collected from subjects in this arm of the study will be batched and tested retrospectively. The clinicians, therefore, will be blinded to the BDG results and can not use the assay to inform treatment decisions. Because BDG test characteristics in SICU patients are not known, an essential aspect of this study is our ability to assess test performance in the population of interest in an unbiased fashion. Patients in the standard care group may receive antifungal prophylaxis and/or treatment at any time based on the discretion of the treating physician.

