**DESCRIPTION OF STUDY END POINTS**

**Primary Endpoints**

1. Feasibility of preemptive monitoring strategy.
2. β-D-glucan test performance in the stand care (empiric therapy) group.
3. Safety and tolerability of preemptive anidulafungin.

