**Statistical Analyses**

Statistical analysis will be performed using SAS software. P values and 95% confidence intervals will be 2-tailed and statistical significance set at the 5% level unless otherwise specified.

*Demographics and Baseline Characteristics*

Demographic and baseline characteristic information will be summarized and compared using the Chi-squared test for discrete variables and one way ANOVA for continuous various to assess any imbalance between treatment groups.

*β-D-glucan Test Characteristics*

β-D-glucan test characteristics, using data collected from standard care group, will be described using sensitivity, specificity, positive and negative predictive values. Proven and probable cases of IFI, as defined by EORTC/MSG criteria (**tables 3 and 4**), will constitute the standard for comparison.

*Feasibility Analysis*

Feasibility will be a description of preemptive protocol adherence, BDG test requests off schedule, and the number of patients withdrawn from the preemptive arm due to the initiation of empiric systemic antifungal therapy in the absence of a positive BDG test.

*Efficacy End-Points*

Development of IFI during the study period will be assessed by the principal investigator (PI) and a second blinded investigator using predefined EORTC/MSG criteria for proven or probable disease. The study period is defined as the time the patient was cared for in the SICU. The proportions of patients developing IFI, and IC specifically, in each group will be compared using Fisher’s exact test. The median ICU stay and number of febrile days while in the ICU will be compared using the Kruskal-Wallis test. Patient mortality, overall and attributed to IFI, will also be summarized by group. Response-to-therapy (RTT) will be determined by the PI and a blinded second investigator. The RTT population will consist of all patients who were underwent BDG monitoring for at least 3 days and received at least 1 dose of systemic antifungal therapy.

*RNA Analyses*

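### BDG accuracy, a primary endpoint, is estimated in an arm given antifungals at discretion, and nothing separates samples or outcomes after treatment starts, so the estimate is not free of treatment-related bias

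*Protocol*

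**What the plan says.** The Protocol's Primary Endpoints list "β-D-glucan test performance in the stand care (empiric therapy) group". Under Statistical Analyses, "β-D-glucan test characteristics, using data collected from standard care group, will be described using sensitivity, specificity, positive and negative predictive values", with EORTC/MSG proven and probable IFI as the reference standard. The same section sets the study period as the time spent in the SICU.

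Under Standard care/empiric therapy group, the Protocol explains that clinicians in this arm do not see BDG results and that "an essential aspect of this study is our ability to assess test performance in the population of interest in an unbiased fashion". The next sentence reads "Patients in the standard care group may receive antifungal prophylaxis and/or treatment at any time based on the discretion of the treating physician". On sampling: "Patients in the standard care arm will also have biweekly blood draws for the BDG assay until ICU discharge".

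The Censoring section names withdrawal of consent as the only reason for censoring. The Data Analysis section puts all primary and secondary analyses on an intent-to-treat basis. No section treats BDG samples or IFI outcomes differently once an antifungal has been started in this arm.

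**The concern.** Clinicians who cannot see BDG cannot act on it, so the arm is protected against treatment driven by the test. They can still act on fever, colonisation or general deterioration, all of which are related to true infection. Study Design describes standard care at this centre as empiric antifungal therapy at physician discretion, so such treatment is expected.

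Treatment can act in two places. First, it can stop an infected patient from ever meeting proven or probable criteria, which corrupts the reference standard. Second, it can lower BDG, which corrupts the index test. Elsewhere the Protocol allows for both:

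- Systemic antifungals in the 7 days before entry are an exclusion.
- In the preemptive arm, "Kinetic monitoring will continue until the test becomes negative".
- Normalisation of BDG is part of the definition of response to preemptive therapy, and the whole of it in Table 5.
- Infections diagnosed after at least 72 hours of antifungals form a separate breakthrough category.
- The footnote on microarray hybridisation requires controls without empiric antifungal therapy.

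The accuracy analysis has no such safeguard. At stake is whether the 60 pg/ml cut-off can guide therapy in a population where, as the Introduction says, the performance of the assay is not established.

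**Working it through.** **Stated figures.** The Sample Size section gives 100 patients randomised 3:1, so 75 and 25. A 25% positive rate gives 75 × 0.25 = 18.75, rounded to the stated 19. These reproduce. The Protocol states no precision or power for BDG accuracy, so what follows is an illustration and does not dispute any stated figure.

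**Inputs.**
- N = 25 (Sample Size).
- Share BDG-positive q = 0.25 (Sample Size), assumed to apply to standard care as well.
- Sensitivity Se = 0.81 at 60 pg/ml (Active surveillance/preemptive therapy group, a cited figure for invasive candidiasis, IC).
- Underlying infection rate π: not given. Assumed 10%, range 5% to 20%. The Introduction mentions 10% only as a threshold for prophylaxis. IC stands in for IFI.
- Masked share m, the cases treated before confirmation that never meet the criteria: not given. Assumed 0, 25% and 50%, regardless of BDG result.

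**Formulas.** Unmasked: TP = Se·πN, FN = πN − TP, FP = qN − TP, TN = N − TP − FN − FP. Masked: TP′ = (1−m)TP, FN′ = (1−m)FN, FP′ = FP + m·TP, TN′ = TN + m·FN.

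**Results at π = 10% (2.5 cases, 6.25 positives).**

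| | m = 0 | m = 25% | m = 50% |
|---|---|---|---|
| TP | 2.025 | 1.519 | 1.0125 |
| FN | 0.475 | 0.356 | 0.2375 |
| FP | 4.225 | 4.731 | 5.2375 |
| TN | 18.275 | 18.394 | 18.5125 |
| Sensitivity | 81% | 81% | 81% |
| Specificity | 81.2% | 79.5% | 77.9% |
| PPV | 32.4% | 24.3% | 16.2% |
| NPV | 97.5% | 98.1% | 98.7% |

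For m = 50%: PPV = 1.0125/6.25, specificity = 18.5125/23.75, NPV = 18.5125/18.75, sensitivity = 1.0125/1.25.

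**Other infection rates.** The number of positives is fixed, so PPV is multiplied by (1−m) at any π. With m = 50%, PPV goes from 16.2% to 8.1% at π = 5%, and from 64.8% to 32.4% at π = 20%.

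**Other specificity.** Fix true specificity at 90%, the figure the Introduction cites from a haematology cohort, in place of the 25% positive rate. With π = 10% and m = 50%, PPV goes from 47.4% to 23.7%, specificity from 90.0% to 86.3% and NPV from 97.7% to 98.9%. If treatment also turns half of the masked positives negative, specificity is 88.4% and PPV 26.9%. Clearance therefore partly offsets the loss of specificity.

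**Sensitivity.** It changes only through a further assumption. Suppose a share u of confirmed cases is treated before the informative sample, and a share c of their positives is lost. Apparent sensitivity is then 0.81 × (1 − uc). With u = c = 25% this is 76%, and with u = c = 50% it is 61%.

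**The case against.** The strongest defence has four parts.

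**Inclusion of on-treatment samples is not stated.** A reader might infer that the Protocol expressly scores them. It does not. That is inferred from sampling to discharge, from use of the arm's data without restriction, and from the Censoring section, which mainly concerns withdrawal and mortality follow-up. Sample eligibility could be settled in an SAP. This stands as a limit on the wording. It does not answer the reference-standard problem: even with pre-treatment samples only, an infected patient treated on suspicion and never confirmed is still scored as uninfected.

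**The unbiased claim may be meant narrowly.** It follows the sentence on blinding, and may mean only that the test cannot drive treatment. On that reading it is true, and using this arm rather than the preemptive arm is sensible. But the text does not say so, and the next sentence opens the other route.

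**Sensitivity may not suffer.** A reader might infer that sensitivity, specificity and PPV are all understated. Removing half of the true positives and none of the false negatives would give 1.0125/(1.0125 + 0.475) = 68%. But clinicians are blinded to BDG, and the documents give no ground for masking only BDG-positive cases; masking regardless of BDG leaves 81%. Clearance before the informative sample is also uncertain. The Introduction cites a median 10-day lead of BDG over diagnosis (haematology cohort), and a later negative would not erase an earlier positive in an ever-positive analysis. The Protocol gives no clearance rate.

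**Imprecision dominates.** At 10% there are about 2.5 cases, the chance of none is 0.9^25 = 7%, and 2 of 2 detected gives a 95% interval of 16% to 100%. The analysis is descriptive. This is correct, but a wide interval neither discloses nor corrects a bias.

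**Conclusion.** The concern holds in limited form. As written, the accuracy analysis is protected against test-driven treatment but not against suspicion-driven treatment, so the stated aim is met only in the narrow sense. Masked infections push specificity and PPV down and NPV up. Sensitivity falls only if treatment clears BDG before the informative sample, or if masking is more common in BDG-positive cases; the documents establish neither.

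The size cannot be determined from the Protocol. The halving of PPV rests on an assumed 50% masked share, and the level it starts from on an assumed infection rate. This is a risk built into the design, not a measured effect. It still merits correction, because the endpoint is primary and one misclassified patient matters among two or three expected cases.

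**What to change.** In Statistical Analyses, under β-D-glucan Test Characteristics:

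1. Base the primary accuracy analysis on samples drawn up to the first dose of any systemic antifungal.
2. Keep as cases all patients with proven or probable IFI, including those treated while results were pending and later confirmed from specimens taken before or around treatment start.
3. Class as reference-standard indeterminate only patients treated on suspicion who never meet the criteria. Report accuracy with all of them counted as infected and with all counted as uninfected.
4. Report the all-data analysis alongside.

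Under Standard care/empiric therapy group, qualify "our ability to assess test performance in the population of interest in an unbiased fashion" as meaning free of treatment driven by the test result.

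On the CRF, record antifungal start dates and BDG sample dates. The Protocol already calls for weekly recording of antimicrobials and for the empiric agent, but does not mention a start date.

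The cost is wording, two date fields, fewer evaluable samples and wider intervals in an arm of 25. The baseline sample should remain usable for nearly all patients, since antifungals in the 7 days before entry are excluded. Clinical management does not change.
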